## Abstract

Background: Complications due to frailty and injury after falls are a significant problem for people living in residential aged care. This can lead to a range of negative outcomes including poor physical, social, and psychological well-being. The Australian Royal Commission into Aged Care Quality and Safety highlighted many aspects of care in residential aged care homes requiring improvement, leading to specific recommendations aimed at improving the outcomes in this area. This contributed to four recommendations calling for increased allied health interventions to meet the unmet needs in residential aged care. This intervention aims to implement and evaluate evidence-based allied health interventions for people living in residential aged care specifically relating to frailty, preventing falls, and maintaining engagement in everyday activities. Method: This is a pragmatic, non-randomised, pre–post design study where six groups of up to 10 residents of an aged care home will start the intervention at staggered times. The EAHOP intervention is an integrated application of a suite of allied health services (occupational therapy, physiotherapy, dietetics, speech pathology, pharmacy, and optometry), with general practitioner involvement, using allied health assistants in an integrated transdisciplinary model of care. The baseline period is 6 weeks, and intervention is a maximum of 36 weeks with follow-up at 12 and 24 weeks. Primary outcomes measure changes in falls, frailty, and quality of life. A qualitative program evaluation will be completed as well as an economic analysis. Conclusion: The results of the study will provide information about the clinical, implementation, and effectiveness outcomes of this integrated, transdisciplinary allied health service model for people living in residential aged care. The results will be used to develop evidence-informed guidelines for residential aged care providers on the delivery of allied health services.

## 1. Background

In Australia in 2023, 185,127 people were living in residential aged care [1] and complications due to frailty and injury after falls are a significant problem for these residents. Following entry into residential care, 3.7% of people are hospitalised due to falls within 90 days, and 9.8% within a year [2]. Every six months, it is estimated that 50% of people with dementia in residential aged care experience a fall [3], leading to significant financial and social costs [4]. Additionally, around 95% of residents are estimated as being frail or pre-frail [5], which is also associated with negative health outcomes resulting in hospitalisation [6]. People living in residential aged care also often find a discontinuity between what they found meaningful and engaging prior to entering aged care and what they experience in care, which adversely affects their quality of life [7]. There is a need to focus on enabling people in residential aged care to keep engaging in activities they find meaningful [8] and maximising engagement in everyday life.

The Royal Commission into Aged Care Quality and Safety heard that only 24% of people living in residential aged care felt their needs were always met across several care experiences [9]. This contributed to four recommendations calling for increased allied health interventions to meet the unmet needs in residential aged care. Recommendation 37 specifically lists allied health as a service that should be provided in residential care. Recommendation 38 lists thirteen allied health professionals providers should employ or retain. Recommendation 61 recommends changes to the Medicare Benefits Schedule to include allied health service provision in residential care. Recommendation 69 states that allied health care should generally be provided by aged care providers.

Allied health has an essential role in meeting the challenges associated with fall prevention, addressing frailty and keeping residents engaged in meaningful activities [8,10]. The Royal Commission received submissions comparing residential aged care in British Columbia where residents receive 22 min of allied health service per day, to Australia where only 2% residents receive this level of service [11]. Even after significant reform following the Royal Commission, there has not been any improvement in the amount of allied health services in residential aged care, and in fact this appears to have further deteriorated [12]. There is a clear and urgent need for a new model of allied health provision in residential aged care.

This intervention aims to implement and evaluate evidence-based allied health interventions for people living in residential aged care specifically related to frailty, preventing falls, and maintaining engagement in everyday activities. The intervention, conducted in partnership with General Practitioners (GPs) and a residential aged care provider, will coordinate an integrated transdisciplinary program (EAHOP intervention) of evidence-based allied health services including occupational therapy, physiotherapy, speech pathology, pharmacy, dietetics, and optometry to older people living in residential care, in conjunction with the nurses and care workers onsite. Allied health assistants will also be involved in delivering transdisciplinary interventions, under the supervision of the relevant allied health professional.

### 1.1. Research Questions

Is an integrated transdisciplinary allied health service model effective in preventing falls, addressing frailty, and promoting engagement in people transitioning to or living in residential aged care?Can an integrated transdisciplinary allied health service model improve outcomes focused on falls, frailty, and engagement, compared to baseline measures, in people transitioning to or living in residential aged care?What are the care experiences of residents, carers, staff, and other key stakeholders when an integrated transdisciplinary allied health service model is implemented in residential aged care?

### 1.2. Objectives

Implement and evaluate a new integrated and transdisciplinary model of allied health intervention in relation to the impact on falls, frailty, engagement, quality of life, and cost-effectiveness.Evaluate the process (or implementation) of the new allied health service model by asking key stakeholders (residents, families, care staff, and nursing staff) about their experiences of participating in the model.Produce evidence-informed guidelines for residential aged care providers in Australia to implement an integrated transdisciplinary allied health service.

## 2. Methods

### 2.1. Study Design

This is a pragmatic, non-randomised, pre–post design study where six groups of up to 10 participants will start the intervention at different times. Each group will commence a baseline period lasting six weeks. Primary outcome measures will be administered in week 0 (−t_1_) of the baseline period and in week 6 (−t_2_) of the baseline period. The allied health professionals will conduct assessments using the secondary outcome measures during the baseline period, making recommendations for consideration at the case conference held with the resident’s usual General Practitioner. The prescribed allied health intervention/s will last a maximum of 36 weeks with primary outcome measures taken during the intervention period at 12 (t_1_), 24 (t_2_), and 36 (t_3_) weeks, then at 12 (t_4_) and 24 (t_5_) weeks post-intervention. The case conferences will take place in week 1 or week 2 of the intervention period. The timing of the secondary outcome measures will vary depending on the mix of interventions chosen by the allied health professional and the participant needs. See the Supplementary file for further details.

### 2.2. Study Setting

The intervention will be conducted in a residential aged care home in Canberra, Australia, with a maximum of 60 residents.

### 2.3. Participants

Any new or existing (permanent) resident of the residential aged care home is eligible. Staff at the home will approach any new or existing resident and/or family with a study flyer. The research team will present the study to the residents at the regular residents’ meeting. Participants will register their interest through a register kept by the nursing staff at the home and/or they will be able to contact the research team through contact details listed on the flyer and promotional material posted at the home. All participants and/or their carers, power of attorney, or guardian will be required to give written consent after reading the relevant participant information at which time the Clinical Liaison Manager (who is a Registered Nurse) will consent them into the study and assign them a study number. Residents with a diagnosis of dementia or identified by care staff as experiencing cognitive impairment are eligible. All participants will be screened for cognitive function using the Psychogeriatric Assessment Scale (PAS) [13]. There is no cutoff score for inclusion; however, in some cases, people with severe cognitive impairment will not be able to engage in the allied health program. For example, people who have severe expressive and receptive communication impairment and who are immobile due to dementia. For those residents with severe dementia or on an end-of-life pathway, we will liaise with the relevant medical team and/or staff Registered Nurse to determine if these residents should ethically be considered for the program. Residents who elect not to participate in the intervention will receive their usual medical, health, and lifestyle services as usual.

Participants will be able to discontinue the intervention at any time at their, or their Enduring Power of Attorney’s, request. Participants will be withdrawn from the study if any deterioration in their medical condition makes participation unsafe in the opinion of their General Practitioner.

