### 2.6. SampleSsize

The sample size was calculated using R based on 1000 simulated versions of the study, where the power estimate is the proportion of simulated studies that gave *p* < α for the difference between the pre- and post-intervention stages. Using the Short Physical Performance Battery (SPPB) as the primary outcome measure with 50 subjects, the increased mean responses anticipated with alpha 0.01 are shown in Table 2. This is assuming the following parameters: average response at baseline 5; between-subject SD 2.5; variability in effect between subjects SD 2 (so the effect is 2.5 with SD of 2); within-subject SD of 1; and between-group SD of 2 [18].

We expect up to 60 existing residents will consent to the intervention. The site estimates that 20 new residents will enter the home during the study period, and we estimate 15 of these new residents will consent to the study. With a 20% dropout and loss to follow-up, the highest number of participants to complete the intervention is 60 participants.

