## 3. Data Analysis

### 3.1. Quantitative Analysis

All statistical analysis will be conducted using R version 4.2.1 (23 June 2022) in Rstudio (version 2023.6.2.561). Baseline demographic and descriptive statistics will be summarised for each group prior to the intervention starting (control phase). Primary outcome measures will be collected twice in the control period at week 0 and week 6. Primary outcome measures will be collected every 12 weeks during the intervention (weeks 12, 24, and 36) and at 12 weeks and 24 weeks post-intervention for each group. Categorical data will be summarised using frequency statistics and will be visualised. Continuous and other numerical data will be visually explored and summarised using sample descriptive statistics, selected as appropriate based on apparent distributions. A mixed-effects model will be computed, with treatment stage (i.e., pre- vs. post-intervention) as a fixed effect and subject as a random effect. Sensitivity analyses will be conducted, which will impute missing data using the “mice” package (version 3.15.0) [34].

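### For new entrants the pre-versus-post contrast is confounded with time since entry, and the 12-month falls pre-window mostly lies before they lived in the home

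*Protocol article*

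**What the plan says.** - **Population.** Section 2.3: "Any new or existing (permanent) resident of the residential aged care home is eligible". No minimum time since entry is given. Section 2.6 expects up to 60 existing residents and 20 arrivals, and of the arrivals "we estimate 15 of these new residents will consent to the study". Both effectiveness questions in Section 1.1 concern effects "in people transitioning to or living in residential aged care".
- **Timing.** Section 2.1: "Each group will commence a baseline period lasting six weeks", and "The prescribed allied health intervention/s will last a maximum of 36 weeks". Section 3.1: "Primary outcome measures will be collected twice in the control period at week 0 and week 6".
- **Falls windows.** Section 2.8 counts falls over the 12 months before enrolment, from the home's own records. Table 3 lists the past 12 months, the intervention period and the period after it. It lists no six-week count.
- **Model.** Section 3.1 specifies a mixed-effects model "with treatment stage (i.e., pre- vs. post-intervention) as a fixed effect and subject as a random effect".
- **Natural course after entry.** Section 1: "3.7% of people are hospitalised due to falls within 90 days, and 9.8% within a year".

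**The concern.** A subject random effect absorbs stable differences between residents. It does not absorb a rate that changes within a resident as the time since moving in grows. For a new entrant, the pre stage is by construction nearer to entry than the post stage. If the early weeks carry a different fall rate, that difference enters the stage coefficient. There is no concurrent control to reveal it. Staggered group starts do not help either, because the clock is each resident's own entry date and not the calendar.

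The falls pre-window is also poorly suited to these residents. A 12-month look-back from the home's records reaches into a time when they lived elsewhere, and the home would not ordinarily hold those falls.

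At stake are the direction and size of a primary outcome in up to a fifth of the sample. So is any statement about people moving into care that rests on an estimate drawn about 80% from existing residents.

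**Working it through.** **Share of new entrants.** (60 + 15) × (1 − 0.20) = 60, which reproduces the completer figure in Section 2.6. New entrants are 15/75 = 20%.

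**Early against later hospitalisation due to falls** (Section 1):
- Linear: 3.7/90 = 0.0411% per day; (9.8 − 3.7)/275 = 0.0222% per day; ratio 1.85 (1.80 to 1.91 allowing for rounding of the inputs).
- Constant hazard within each period: −ln(0.963)/90 = 0.000419; −ln(0.902/0.963)/275 = 0.000238; ratio 1.76.

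**Reading A: six-week baseline count as comparator.** This assumes no intervention effect, all falls following the ratio above with a single step at day 90, and existing residents at the later rate throughout. The later rate is set to 1.
- Baseline on days 0–42, intervention on days 42–294, of which 48 days are early and 204 later. Mean intervention rate: (48 × 1.85 + 204)/252 = 1.16. Ratio to baseline: 1.16/1.85 = 0.63 (0.65 on the hazard scale).
- Baseline on days 48–90, intervention wholly after day 90: 1/1.85 = 0.54 (hazard 0.57).
- Pooled, 20% new entrants. Start on day 0: (0.2 × 1.163 + 0.8)/(0.2 × 1.853 + 0.8) = 0.88 (hazard 0.89). Start on day 48: 1/(0.2 × 1.853 + 0.8) = 0.85 (hazard 0.87).

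| Baseline starts, days after entry | New entrants, intervention ÷ baseline | Pooled |
|---|---|---|
| 0 | 0.63 to 0.65 | 0.88 to 0.89 |
| 48 | 0.54 to 0.57 | 0.85 to 0.87 |
| 90 or later | 1.00 | 1.00 |

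**Reading B: 12-month look-back, not scaled to time in the home.** Enrolment s days after entry leaves s/365 of the window in the home: 0% at entry and 90/365 = 25% at day 90. If the home holds no earlier falls, the apparent pre-rate at day 90 is 0.247 × 1.76 to 0.247 × 1.85 = 0.43 to 0.46 of the later rate. The undercount outweighs the early excess, so falls appear to rise.

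**Reading C: 12-month look-back, scaled to days in the home.** For enrolment by day 90 the observed pre-time lies wholly in the early period, so the direction is again a drop. The pooled size is not given by Reading A, because new entrants contribute far less pre-time than existing residents. Nor does the effect vanish at day 90, since the window still reaches back to the early weeks.

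**The case against.** The strongest reply is that Reading A is not the written plan. Section 2.8 and Table 3 name the past 12 months, and only the placing of primary measures at weeks 0 and 6 makes a six-week count possible. That stands. A reader might infer that falls will drop without any effect; the documents do not support this, because under the written window, unscaled, the bias runs the other way.

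Second, the Background gives people hospitalised due to falls, not fall rates. Reading 1.8 as the document's own figure for fall risk goes too far. Deaths and exits also thin the later denominator, although they would bring the ratio to 1 only if the average share at risk in days 91–365 were about 54% to 57% of that in days 0–90 (1/1.85 and 1/1.76). Early first events in the frailest could produce a declining curve with no change within any resident, and within-resident change is what the model estimates. So the ratio is suggestive and does not prove a within-resident trend.

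Third, the 11% to 15% needs all 15 entrants to start baseline by day 48. The article gives no interval from entry to baseline, and consent and staggered group starts take time. That stands, and the figure is an upper range.

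Fourth, covariates are commonly left to an analysis plan, and the stated model does not forbid more terms. This is fair, but the article itself fixes the contrast, the mixed population and a pre-window that does not fit part of that population.

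A reader might also infer a pre-post bias in hospital leave days. The only comparison described for these, in Section 2.10, is with a sample matched on age, sex and level, so that inference is not supported.

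**Conclusion.** The point holds in a limited form. For about 15 of 75 expected participants, stage is confounded with time since entry, and the stated model does not separate them. The falls pre-window is unsound for the same residents. The direction of the bias depends on a choice the article leaves unclear: towards a rise with an unscaled 12-month count, towards a drop with a scaled count or a six-week count.

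On the six-week reading the pooled artefact is at most about 11% to 15%, and nil if entrants start baseline after day 90. That size rests on hospitalisation due to falls standing in for all falls, on a single step at day 90, and on existing residents staying at the later rate. The confounding itself needs only a fall rate that changes after entry, and the pre-window problem does not depend on the 1.8 at all.

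**What to change.** 1. State one falls pre-window, the same in Sections 2.1, 2.8, 3.1 and Table 3, and analyse falls as a rate per person-time in the home. This also corrects the window for existing residents with less than a year's stay.
2. Add time since entry (up to 90 days against later, time-varying) to the falls model, or estimate new and existing residents separately.
3. Base any statement about people moving into care on the new-entrant stratum.
4. For the hospital-leave comparison in Section 2.10, match on or adjust for time since entry if the comparison data hold it.

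The cost is analysis wording plus entry dates, which the home should hold; recruitment and care do not change. With about 15 entrants their own estimate will be imprecise. Where an entrant's baseline lies wholly before day 90 and the intervention wholly after it, the time-since-entry term can be separated from stage only by assuming the same intervention effect as in existing residents, and the report should say so. Leaving new entrants out of the main contrast would also remove the confounding, but Section 1.1 names them in both effectiveness questions, so that is a debatable trade-off and not needed here.

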### 2.4. Conceptual and Operational Framework

#### 2.4.1. Model of Care

The EAHOP intervention has been designed following the Institute for Healthcare Improvement [14] 4Ms framework of an age-friendly health system as the model of care to organise allied health interventions. The 4Ms are as follows:What Matters: Know and align care with each older adult’s goals and care preferences.Mentation: Prevent, identify, treat and manage dementia, depression, and delirium across care settings.Medication: If medication is necessary, it should not interfere with What Matters to the older person.Mobility: Ensure that older people move safely every day.

#### 2.4.2. Case Conferencing

The allied health professionals will conduct their discipline-specific, secondary outcome measures during the baseline period and then make recommendations to be discussed at a case conference. The case conference will be attended by the resident’s General Practitioner, the research clinical liaison manager, and where possible the resident and family member. A plan of action will be agreed with the resident and their family following the case conference that could involve one or more allied health interventions depending on the needs of the resident.

#### 2.4.3. Clinical Liaison Manager

A Clinical Liaison Manager (Registered Nurse) will be embedded within the aged care home with the overall goal of ensuring the case conferences and interventions are implemented as intended, managing data collection and providing a central point of contact for communication between the participants and their family members, aged care team, the embedded allied health team, and the research team.

#### 2.4.4. Allied Health Professionals and General Practitioner

There are six allied health professionals, a dietitian, pharmacist, physiotherapist, occupational therapist, optometrist, and speech pathologist, who will conduct discipline-specific assessments and provide discipline-specific interventions as needed, as identified and agreed in the case conference with a General Practitioner assisting with the coordination of care.

#### 2.4.5. Allied Health Assistants

Allied health assistants will work directly with five of the allied health professionals (dietitian, occupational therapist, physiotherapist, dietitian, and speech pathologist) to implement the prescribed allied health interventions.

See Figure 1 for a diagrammatical representation of the EAHOP intervention. 

### 2.5. Intervention

A brief description of the discipline-specific interventions is described in Table 1.

#### Action Falls Program

In addition to the allied health interventions for individual participants (described in Table 1), the intervention will also involve an organisational intervention through implementation of the Action Falls program [17]. An Action Falls checklist will be completed with each participant (and or carer/family member, as appropriate). The Clinical Liaison Manager, who will receive formal training in the implementation of the Action Falls Program, will oversee the completion of the checklist, which can be carried out by any member of the team or residential aged care staff once training is complete.

### 2.6. SampleSsize

The sample size was calculated using R based on 1000 simulated versions of the study, where the power estimate is the proportion of simulated studies that gave *p* < α for the difference between the pre- and post-intervention stages. Using the Short Physical Performance Battery (SPPB) as the primary outcome measure with 50 subjects, the increased mean responses anticipated with alpha 0.01 are shown in Table 2. This is assuming the following parameters: average response at baseline 5; between-subject SD 2.5; variability in effect between subjects SD 2 (so the effect is 2.5 with SD of 2); within-subject SD of 1; and between-group SD of 2 [18].

We expect up to 60 existing residents will consent to the intervention. The site estimates that 20 new residents will enter the home during the study period, and we estimate 15 of these new residents will consent to the study. With a 20% dropout and loss to follow-up, the highest number of participants to complete the intervention is 60 participants.

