### 2.8. Outcome Measures

Primary outcome measures are the number of residents who fall (falls) and the number of falls for each participant (fall rate) in 12 months prior to enrollment in the project. All falls are recorded by the residential aged care home and these data will be accessed by the research team. Other outcome measures are the Quality of Life Aged Care Consumers tool (QOL-ACC) [19], The Frail in Nursing Homes (Frail-NH) Scale [20], and the Short-Form Physical Performance Battery (SPPB) [21]. Each allied health discipline has discipline specific outcome measures that are secondary outcome measures along with a measure of pain. See Table 3.

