Optometry	Participants will receive an onsite, mobile assessment by an optometrist evaluating visual function (including refraction, confrontation fields, visual acuity, ocular structure (macula and optic nerve lenticular assessment, and intra-ocular pressure) to address visual impairments that may contribute to fall risk. Actions arising from the assessment of visual function may include new spectacle prescriptions or referral of participants for management of ocular disease.
Pharmacy	Participants will receive an onsite medication review by a pharmacist who will provide recommendations regarding the resident’s medication to the participant’s GP, nursing staff, and family members. After the initial medication review, participants will receive a 2-week follow-up visit to understand how medication decisions are implemented in the medication treatment and charts. Each participant will have an initial case conference and then a follow-up visit from the pharmacist every 3 months (online or in person).

**Table 2 healthcare-13-00341-t002:** Associated power based upon *n* = 50 and mean change in the SPPB.

Increase Mean Response After Intervention	Power
2.5	0.99
2	0.94
1.75	0.84
1	0.63

**Table 3 healthcare-13-00341-t003:** Outcome measure summary.

Primary Outcome Measures	
Falls: Number of falls in past 12 months Number of falls during intervention period Number of falls after intervention	
Quality of Life Aged Care Consumers (QOL-ACC) [19]	
Frailty: The Frail in Nursing Homes (Frail-NH) Scale [20] and the and Patient Health Questionnaire (PHQ9) [22]	
Short Physical Performance Battery (SPPB) [21]	
**Secondary outcome measures**	**Allied health discipline**
Short Falls Efficacy Scale—International (Short FES-I) [23]	Physiotherapy
Subjective Global Assessment (SGA) [24] Mid-arm muscle circumference [25,26] Quantitative analysis of dietary intake will be calculated before and after fortification	Nutrition and Dietetics
Canadian Occupational Performance Measure (COPM) [27]	Occupational Therapy
Number of medications (that contributed to increased risk of falls) ceased/changed at case conferences Number of case conferences and pharmacist follow-ups Rate of GP agreement on pharmacist recommendations	Pharmacy
Number of new or updated spectacles recommended Number of referrals arising from vision assessment The National Eye Institute Visual Functioning Questionnaire—25 (VFQ-25 + 10) [28]	Optometry

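### The primary outcome is named inconsistently (SPPB in Section 2.6, falls in Section 2.8, at least five measures in Table 3), so the stated power does not cover falls and the trial-level false-positive rate depends on the list used

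*Protocol article*

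**What the plan says.** Four places in the protocol article speak to the primary outcome.

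- **Abstract:** "Primary outcomes measure changes in falls, frailty, and quality of life". These are domains, and physical performance is not among them.
- **Section 2.6:** power is calculated "Using the Short Physical Performance Battery (SPPB) as the primary outcome measure with 50 subjects", at alpha 0.01. Table 2 gives the results.
- **Section 2.8:** "Primary outcome measures are the number of residents who fall (falls) and the number of falls for each participant (fall rate"), with the window "in 12 months prior to enrollment in the project". The next sentence begins "Other outcome measures are the Quality of Life Aged Care Consumers tool (QOL-ACC"), goes on to Frail-NH, and ends "and the Short-Form Physical Performance Battery (SPPB) [21]". The section then calls the discipline-specific measures and pain secondary, and points to Table 3.
- **Table 3, primary block:** falls (in the past 12 months, during the intervention and after it), QOL-ACC, "Frailty: The Frail in Nursing Homes (Frail-NH) Scale [20] and the and Patient Health Questionnaire (PHQ9) [22]", and "Short Physical Performance Battery (SPPB) [21]".

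Section 3.1 describes one mixed-effects model with treatment stage as a fixed effect and subject as a random effect. It does not tie the model or the 0.01 level to a particular outcome.

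**The concern.** The study is non-randomised, at one site, and compares before with after. A primary outcome fixed in advance is one of its main safeguards against selective reporting. If the text supports more than one primary outcome, whichever result looks best can later be presented as the planned one, with the document to back it.

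Two further consequences follow. The only power figures belong to SPPB, so a reader who takes falls as primary from Section 2.8 has no power figure for the outcome that matters. And the number of primary tests, which sets the trial-level false-positive rate, changes with the section one reads.

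The falls definition in Section 2.8 has its own fault. A count over the 12 months before enrolment is fixed before any treatment starts and cannot by itself show an effect.

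**Working it through.** **Step 1. The lists side by side.**

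| Measure | Abstract | 2.6 | 2.8 | Table 3 |
|---|---|---|---|---|
| Falls | primary (domain) | – | primary (fallers; rate) | primary |
| QOL-ACC | primary (domain) | – | other | primary |
| Frail-NH | primary (domain) | – | other | primary |
| PHQ9 | – | – | – | primary, in the frailty row |
| SPPB | – | primary, alone | other | primary |

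Taken literally, no two columns agree. PHQ9 is named only in Table 3.

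**Step 2. What the stated power covers.** Table 2 gives 0.99, 0.94, 0.84 and 0.63 for mean SPPB increases of 2.5, 2, 1.75 and 1, with n = 50 and alpha 0.01.

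I tried to reproduce these with power = Φ(δ/SE − 2.576), two-sided.

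- Paired, one pre and one post measure, using the stated effect SD of 2 and within-subject SD of 1: SE = √((2² + 1 + 1)/50) = 0.346. Power is 1.00, 0.999, 0.993 and 0.622.
- Two-sample with SD 2.5: SE = √(2 × 2.5²/50) = 0.500. Power is 0.992, 0.923, 0.822 and 0.282.

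The first version matches the rows for 2.5 and 1. The second matches the first three rows within 0.02. No variant tried matches all four. That is a separate matter from this point. What matters here is that every input and every row concerns change in SPPB, and none of it transfers to a count of falls or to a proportion of fallers.

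**Step 3. Trial-level false-positive rate.** For k independent tests at the stated 0.01, the chance of at least one false positive is 1 − 0.99^k.

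- SPPB alone (2.6), k = 1: 0.010
- Two falls measures (2.8), k = 2: 0.020
- Three domains (abstract), k = 3, one test per domain: 0.030
- Falls, QOL-ACC, Frail-NH, PHQ9 and SPPB (Table 3), k = 5 with falls as one test: 0.049

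Positive correlation between outcomes lowers these values. The Bonferroni sum (0.05 for k = 5) is the upper bound.

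**Step 4. Illustration of falls power.** The document gives no falls rate for this population. Assumptions:

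- 50% of residents fall in six months (Background, given there for residents with dementia);
- Poisson counts at a constant rate, without overdispersion, and independent periods;
- n = 50, with 12 months before compared with 36 weeks during the intervention;
- two-sided 0.01.

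Rate = −ln(0.5)/0.5 = 1.386 falls per resident-year. Expected falls before: 50 × 1.386 = 69.3. During: 69.3 × 36/52 × RR = 48.0 × RR. SE(log RR) = √(1/69.3 + 1/(48.0 × RR)), and power = Φ(|ln RR|/SE − 2.576).

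- RR 0.7: SE = √(1/69.3 + 1/33.6) = 0.210; 0.357/0.210 = 1.70; power 0.19
- RR 0.6: SE = √(1/69.3 + 1/28.8) = 0.222; 0.511/0.222 = 2.30; power 0.39
- RR 0.5: SE = √(1/69.3 + 1/24.0) = 0.237; 0.693/0.237 = 2.93; power 0.64

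The assumed rate matters. Halving it multiplies the SE by √2, and power becomes 0.08 (RR 0.7) and 0.31 (RR 0.5). Doubling it divides the SE by √2, and power becomes 0.43 and 0.94. Overdispersion would lower all of these.

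**The case against.** The fairest defence is that the lists are looser than they are contradictory. The abstract may summarise Table 3 by domain. In Section 2.8 the word other may mean other primary, because only the discipline measures and pain are then called secondary and the reader is sent to Table 3. Section 2.6 may simply have picked one of several primary outcomes for sizing. The visit schedule in Sections 2.1 and 3.1 also fits instruments better than a yearly falls count.

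The abstract reading is plausible, so calling all four lists mutually incompatible would go too far. The reading of other is possible too. Even with both granted, Section 2.6 still speaks of SPPB as the one primary measure, and PHQ9 is primary in Table 3 but absent from Section 2.8. An unseen analysis plan would not remove this, because the text shown states the point in conflicting ways.

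Several stronger inferences are not supported:

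- **That no error rate is defined at all.** Section 2.6 states 0.01 for SPPB. Only the trial-level rate is open.
- **That the error rate is about 23%.** That value comes from five independent tests at 0.05 each, a level the document does not use.
- **That falls power is known to be 19%.** The rate behind it is given for residents with dementia, whereas any permanent resident is eligible. The Poisson form is also my assumption.
- **That five outcomes at 0.01 each is the intended design.** 0.05/5 = 0.01 fits, but the document never says so.

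**Conclusion.** The point holds as an inconsistency in the document's own text. Sections 2.6, 2.8 and Table 3 do not agree on what is primary. The stated power, 0.63 to 0.99 across the whole of Table 2, belongs to SPPB only. At the stated 0.01 with independent tests, the trial-level false-positive rate lies between 1% and 4.9% depending on the list, so it is modest if 0.01 governs every primary test. The larger risk is that the confirmatory result could be chosen after the data are seen. The falls window in Section 2.8 is wrong as written for an effect measure. The falls power figures show only that SPPB power cannot stand in for falls power; they do not estimate this trial's power.

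**What to change.** Before outcomes are analysed:

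1. The sponsor fixes one primary outcome, or one set with a stated alpha split (0.01 each for five would be one example), and uses it identically in the abstract, Section 2.6, Section 2.8 and Table 3. The choice is the sponsor's, and it should settle the status of PHQ9 and of number of fallers against fall rate.
2. Section 3.1 states which tests the 0.01 level governs.
3. Section 2.8 defines the falls outcome as a comparison of pre-enrolment falls with falls during and after the intervention, in line with the three counts in Table 3.
4. Table 2 is labelled as power for SPPB only.
5. If falls stay primary, their power is stated with the assumed rate, distribution and periods.

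The cost is wording and one further power figure, probably less favourable than Table 2. No new data are needed.
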